| Statistical methods:                                                                                                                                         | 
The main objective of the trial is to contribute information on the size of induration in a healthy BCG vaccinated population, which can be used to define an optimal cut-off point for a C-Tb skin test.
 
In the trial the specificity of C-Tb (Specx) as a function of x (the diameter of the induration in mm) will be estimated.
 
For each (integer) value of x, Specx is estimated by the relative frequency of volunteers in the trial with a C-Tb induration ≤ x mm. 95% confidence intervals for Specx are obtained as Specx ± 2 × √ (Specx × (1 - Specx) / n), where n is the number of validly included volunteers.
 
As BCG vaccinated healthy subjects are not supposed to get an induration when exposed to C-Tb no formal statistical comparison of induration sizes between C-Tb and PPD will be made.
 
The subjects will have their PPD indurations classified according to UK standards for PPD cut-off points: 0-5 mm, 6-14 mm and 15+ mm (The Green Book).
 
PPD is considered negative if the induration is < 6 mm.
 
www.dh.gov.uk/en/PublicHealth/Healthprotection/Immunisation/Greenbook/DH_4097254
 |                                             |

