## **7 Trial objectives**

### **7.1 Primary objectives**

- To assess the specificity of the C-Tb test as a function of the cut-off value (i.e., the smallest size of induration measured in mm resulting in a positive outcome of the C-Tb test) when the test is administered intradermally by the Mantoux technique to healthy BCG vaccinated adults.

The specificity of the C-Tb test is defined as the relative frequency of subjects in a healthy population (i.e., no exposure to MTb) who have an induration response < cut-off after a C-Tb

test, whereas the sensitivity is defined as the relative frequency of patients with an induration response  $\geq$  cut-off in TB patients.

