# 8 Investigational plan

## 8.1 Overall design

This clinical trial is a single-centre phase IIa study designed to investigate the specificity of C-Tb under various definitions of cut-off in a double blind randomised, split-body study comparing 0.1  $\mu$ g/0.1 mL C-Tb with the reference agent 2 T.U. Tuberculin PPD RT 23 SSI (Each volunteer receives the C-Tb agent in one arm and the 2 T.U. Tuberculin PPD RT 23 SSI agent in the other arm). The two skin tests are administered in a double-blind manner to make topical readings of an induration, if any, as objective as possible.

The trial will be conducted at Surrey Clinical Research Centre, University of Surrey, Guildford, United Kingdom under the responsibility of Principal Investigator: [name] [name].

The primary objective of the trial is to assess the specificity of the C-Tb skin test agent defined as the relative frequency of subjects in a healthy population (i.e., no exposure to MTb) who have an induration response  $<$  cut-off after a C-Tb test.

The C-Tb skin test is developed from MTb specific antigens (ESAT-6 and CFP-10) which are not expressed by any of the BCG-strains and only by a few of the atypical mycobacteria (e.g., *M. kansasii*, *M. marinum*, *M. szulgai*). No skin reaction (induration) is therefore expected at the injection sites with C-Tb. PPD, however, has protein components that are shared by the BCG vaccine strains and many non-tuberculous/ environmental mycobacteria. Some skin reactions are therefore expected to occur after testing with 2 T.U. Tuberculin PPD RT 23 SSI in a trial population of BCG vaccinated individuals.

Both erythema and induration, if any, will be documented in the case record forms (CRFs) of the volunteers.

In addition to the above, the immune response will be evaluated together with an assessment of the safety of the C-Tb skin test agent.

The volunteers are monitored closely for the occurrence of immediate adverse reactions during the first hour after the injections.

Each trial volunteer will be followed 28 days after the skin test injections and is expected to complete a total of 4 trial visits, as follows:

- |                |                |                                                                                                                                                              |

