### 8.3 Number of subjects

150 healthy BCG vaccinated male and female volunteers between 18 and 65 years of age.

At least 20 % of all included subjects must be < 40 years of age.

At least 20% of all included subjects must be  $\geq$  40 years of age.

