## 12.6 Sample size determinations

The focus of the study is the estimation of  $F^-(x)$ . Power calculations are therefore not relevant for the sample size calculations. The sample size is instead based on the precision of the estimate  $\hat{F}^-(x)$  of  $F^-(x)$ .

From the binomial distribution the variance of  $\hat{F}^-(x)$  is  $\text{Var}(\hat{F}^-(x)) = \hat{F}^-(x)(1 - \hat{F}^-(x))/n$ . An approximate 95% confidence interval for fixed  $x$  is therefore  $\hat{F}^-(x) \pm 2\sqrt{\hat{F}^-(x)(1 - \hat{F}^-(x))/n}$ , where  $n$  is the number of subjects in the group.

The highest value of  $\text{Var}(\hat{F}^-(x))$  ( $= 0.5 / \sqrt{n}$ ) is obtained if  $F(x) = 0.5$ .

The table below shows the standard deviation  $\text{SD}(\hat{F}^-(x))$  as a function of  $F^-(x)$  for  $n=100$ , 150 and 200.

| $F^-(x)$ | Number of subjects ( $n$ ) |       |       |
|----------|----------------------------|-------|-------|
|          | 100                        | 150   | 200   |
| 0.5      | 0.050                      | 0.041 | 0.035 |
| 0.8      | 0.040                      | 0.033 | 0.028 |
| 0.9      | 0.030                      | 0.024 | 0.021 |

With 150 subjects in the trial  $\hat{F}^-(x)$  will always be estimated with a standard deviation  $\leq 0.041$

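### The ±2 SE interval fixed for specificity fails near 100%, where the protocol expects C-Tb results to fall

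*Protocol*

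**What the plan says.** The primary objective (section 7.1) is "To assess the specificity of the C-Tb test as a function of the cut-off value". The Synopsis, under Statistical methods, estimates Spec_x for each integer x by the proportion of volunteers with a C-Tb induration of x mm or less. It fixes the interval as "95% confidence intervals for Spec x are obtained as Spec x ± 2 × √ (Spec x × (1 - Spec x ) / n"; the sample size in the formula counts only volunteers whose inclusion was valid. Section 12.6 gives the same formula for the distribution function of induration, introduced with "An approximate 95% confidence interval for fixed" x. No exact, score or boundary-adjusted interval appears in the protocol, and there is no rule for a sample with no reactors or for a limit above 1.

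On the expected result, section 8.1 says "No skin reaction (induration) is therefore expected at the injection sites with C-Tb". The Synopsis entry that contains the formula gives the same expectation ("As BCG vaccinated healthy subjects are not supposed to get an induration when exposed to C-Tb") as its reason for making no formal comparison with PPD. Section 8.6 excludes QuantiFERON-positive volunteers.

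The planned size in section 8.3 is "150 healthy BCG vaccinated male and female volunteers between 18 and 65 years of age". Section 12.6 justifies it by the standard deviation of the estimate, tabulated at true values of 0.5, 0.8 and 0.9.

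**The concern.** The Wald interval takes its width from p̂(1 − p̂), which goes to zero as p̂ approaches 1. On the protocol's own reasoning, most cut-offs will give a p̂ at or near 1. The formula is therefore weakest at the result the trial is designed to see, and at exactly 100% negative it has no width whatever the true specificity.

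This is the only interval specified for the primary objective. If it is used as written, the report may show several adjacent cut-offs with a 95% interval of 100% to 100%, and others with lower limits that are too high. Readers who weigh these results against the sensitivity data from TESEC-04 would see less uncertainty about specificity than 150 people can support.

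**Working it through.** **Inputs.** n = 150 (section 8.3). Interval p̂ ± 2√(p̂(1 − p̂)/n) (Synopsis and section 12.6). The protocol gives no numerical true specificity, so 0.90 to 0.999 is an assumed range.

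**1. The protocol's own figures.** SD = √(F(1 − F)/n). At n = 150 this gives 0.0408, 0.0327 and 0.0245 for F = 0.5, 0.8 and 0.9, against 0.041, 0.033 and 0.024 printed. The columns for 100 and 200 also reproduce. The table is right as far as it goes, but it stops at 0.9. Section 12.6 also calls 0.5/√n the highest variance. That is the highest SD; the highest variance is 0.25/n.

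**2. Limits by observed count, n = 150.** Two worked cases:

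- 149/150: p̂ = 0.99333 and SE = √(0.99333 × 0.00667/150) = 0.00664, so the interval is 0.99333 ± 0.01329, or 0.980 to 1.007.
- 150/150: SE = 0, so the interval is 1 to 1. The Clopper-Pearson lower limit is 0.025^(1/150) = 0.9757.

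| Negative | Protocol ±2 SE | Clopper-Pearson | Wilson |
|---|---|---|---|
| 150 | 1.000 to 1.000 | 0.976 to 1.000 | 0.975 to 1.000 |
| 149 | 0.980 to 1.007 | 0.963 to 0.9998 | 0.963 to 0.999 |
| 148 | 0.968 to 1.005 | 0.953 to 0.998 | 0.953 to 0.996 |
| 147 | 0.957 to 1.003 | 0.943 to 0.996 | 0.943 to 0.993 |
| 145 | 0.937 to 0.996 | 0.924 to 0.989 | 0.924 to 0.986 |

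The protocol's lower limit is 1.3 to 2.4 percentage points above the exact one.

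**3. Actual coverage, n = 150.** For each true p, the binomial probabilities are summed over the counts whose interval contains p.

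| True specificity | P(all 150 negative) = p^150 | Protocol ±2 SE | Clopper-Pearson | Wilson |
|---|---|---|---|---|
| 0.90 | 0.0% | 92.6% | 97.2% | 96.0% |
| 0.95 | 0.05% | 93.7% | 96.3% | 94.3% |
| 0.97 | 1.0% | 93.6% | 97.4% | 95.2% |
| 0.98 | 4.8% | 80.0% | 98.9% | 96.8% |
| 0.985 | 10.4% | 89.4% | 99.2% | 97.4% |
| 0.99 | 22.1% | 77.8% | 98.2% | 93.5% |
| 0.995 | 47.1% | 52.8% | 99.3% | 96.0% |
| 0.998 | 74.1% | 25.9% | 99.6% | 96.3% |
| 0.999 | 86.1% | 13.9% | 99.0% | 86.1% |

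The dip at 0.98 comes from the discrete counts: the lower limit at 149/150 is 0.98004, just above 0.98, so that count (probability 14.8%) is a miss as well as 150/150 (4.8%). Above 0.98004 the only count whose lower limit exceeds the truth is 150/150, so almost all the non-coverage is p^150. That exceeds 10% once p > 0.1^(1/150) = 0.985.

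**4. Direction of the misses.** At 0.99, 22.1 of the 22.2 percentage points of non-coverage are lower limits above the truth; at 0.98 it is 19.6 of 20.0. A multiplier of 1.96 in place of 2 leaves the coverage unchanged at every tabulated value at which it was tried (all except 0.998).

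**The case against.** The strongest reply is that these intervals are descriptive. There is no hypothesis test, performance threshold or success criterion for specificity. The cut-off is to be chosen by combining the two studies on a ROC curve (sections 6 and 9.3.1), and no confidence limit formally enters that choice. Point estimates are the same under any interval method. The gap in the lower limit is at most 2.4 percentage points, and limits above 1 would normally be truncated in a report. Severe under-coverage needs a true specificity of about 0.98 or more, for which the protocol offers only words; from 0.90 to 0.97 coverage is about 93%. Section 12.6 calls the interval approximate. Its statement that the SD never exceeds 0.041 holds for every true value, so the sample size stands.

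All of this is correct, and it limits the harm to misreported precision. The variance label is a clerical slip with no consequence for the table. It is also fair that Wilson is not a full substitute for the exact method: its coverage is 93.5% at 0.99 and 86.1% at 0.999.

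The defect remains. At 150/150, the result the protocol's rationale points to, the formula gives zero width whatever the truth. An interval covering 53% to 78% is not approximately 95%, and truncating at 1 does nothing for the lower limit. The SD bound of 0.041 is valid, but it says nothing about how the stated interval behaves near 1.

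**Conclusion.** The concern holds. The protocol names one interval for its primary estimate, and that interval fails in the range the protocol expects. At 150/150 it reports a lower limit of 100% where the data support 97.6%; at 147 to 149 negatives it gives impossible upper limits. Coverage is mildly low for true specificities of 0.90 to 0.97, and about 78% at 0.99 and 53% at 0.995, with the error almost entirely in the test's favour.

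The limits by count follow from n = 150 alone; a smaller number of valid volunteers would change them. The coverage figures also depend on an assumed true specificity. The point estimates, the sample size and the ROC method are untouched. The statistical analysis plan was not available and may name another interval, but the protocol states this one explicitly. It should be corrected before the analysis.

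**What to change.** - In the Synopsis and section 12.6, replace the ±2 SE formula with two-sided 95% Clopper-Pearson intervals for every Spec_x. Wilson score intervals are an acceptable alternative if shorter intervals are preferred and coverage somewhat below 95% at some values very close to 1 is accepted. Name one method and carry it into the statistical analysis plan.
- Extend the planning precision in section 12.6 to specificities of 0.95 to 1.00, stated as intervals. For example, 150/150 gives 97.6% to 100% and 147/150 gives 94.3% to 99.6%.
- In section 12.6, label 0.5/√n as the maximum standard deviation.

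The cost is a few sentences. No volunteers, visits or measurements are added. Reported lower limits fall by about 1.3 to 2.4 percentage points for 145 to 150 negatives out of 150.

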## Appendices

Appendix 1: Declaration of Helsinki

Appendix 2: Indemnity Statement

Appendix 3: CIOMS form

Appendix 4: Insurance certificate

### 3 List of Abbreviations and Definitions

|               |                                                                         |
|---------------|-------------------------------------------------------------------------|
| ADR           | Adverse Drug Reaction                                                   |
| AE            | Adverse Event                                                           |
| AFB           | Acid fast bacteria                                                      |
| ALP           | Alkaline Phosphatase                                                    |
| ALT           | Alanine aminotransferase                                                |
| AR            | Adverse Reaction                                                        |
| AST           | Aspartate aminotransferase                                              |
| BCG           | Bacille Calmette-Guérin                                                 |
| CA            | Competent Authority                                                     |
| CFP-10        | 10 kDa Culture Filtrate Protein                                         |
| CI            | Confidence Interval                                                     |
| CIOMS         | Council for International Organizations of Medical Sciences             |
| CRA           | Clinical Research Associate                                             |
| CRC           | Clinical Research Centre                                                |
| CRF           | Case Record Form                                                        |
| CTA           | Clinical Trial Application                                              |
| C-Tb          | rdESAT-6 + rCFP10                                                       |
| Cut-off       | The smallest induration diameter (mm) resulting in a positive C-Tb test |
| DOB           | Date of Birth                                                           |
| DTH           | Delayed Type Hypersensitivity                                           |
| DSMB          | Data safety monitoring board                                            |
| DSMP          | Data safety monitoring plan                                             |
| EC            | Ethics Committee                                                        |
| ESAT-6        | 6 kDa Early Secretory Antigenic Target                                  |
| FPFV          | First Volunteer First Visit                                             |
| GCP           | Good Clinical Practice                                                  |
| GMP           | Good Manufacturing Practice                                             |
| HIV           | Human Immunodeficiency Virus                                            |
| IB            | Investigators Brochure                                                  |
| ICH-GCP       | The International Conference on Harmonisation of Good Clinical Practice |
| IMPD          | Investigational medicinal product dossier                               |
| IF            | Investigators File                                                      |
| IFN- $\gamma$ | Interferon gamma                                                        |
| LPLV          | Last Volunteer Last Visit                                               |
| MHRA          | Medicines and Healthcare products Regulatory Agency                     |
| MTb           | Mycobacterium tuberculosis                                       |
| NCS           | Not clinically significant                                              |

[figure not shown]

|             |                                                                                                |
|-------------|------------------------------------------------------------------------------------------------|
| Ph. Eur     | The European Pharmacopoeia                                                                     |
| PPD         | Purified Protein Derivative                                                                    |
| PPD RT 23   | Purified Protein Derivative Rinsed Tuberculin (batch) 23                                       |
| QFT         | QuantiFERON ® -TB Gold In Tube assay                                                |
| QP          | Qualified Person                                                                               |
| QPPV        | Qualified Person for Pharmacovigilance                                                         |
| rCFP-10     | Recombinant 10kDa Culture Filtrate Protein                                                     |
| rdESAT-6    | Recombinant dimer of 6 kDa Early Secreted Antigen Target                                       |
| RBC         | Red blood cell count                                                                           |
| REC         | Research Ethics Committee                                                                      |
| RGN         | Registered General Nurse                                                                       |
| ROC         | Receiver operating characteristic                                                              |
| SAE         | Serious Adverse Event                                                                          |
| SAR         | Suspected adverse (drug) reaction                                                              |
| Sensitivity | The probability that a test result is positive given the subject has the disease [1]           |
| SmPC        | Summaries of Product Characteristics                                                           |
| Specificity | The probability that a test result is negative given the subject does not have the disease [1] |
| SSI         | Statens Serum Institut, Denmark                                                                |
| SSAR        | Serious Suspected Adverse Reaction                                                             |
| SUSAR       | Suspected Unexpected Serious Adverse (drug) Reaction                                           |
| TB          | Tuberculosis                                                                                   |
| TDL         | The Doctor's Laboratory                                                                        |
| TMF         | Trial master file                                                                              |
| TST         | Tuberculin Skin Test                                                                           |
| WBC         | White blood cell count                                                                         |
| WHO         | World Health Organisation                                                                      |

[figure not shown]

## 6 Introduction

Tuberculosis (TB) continues to be a major cause of morbidity and mortality throughout the world. The disease is caused by infection with *Mycobacterium tuberculosis* (MTb), an intracellular pathogen with one of the most devastating global impacts. WHO estimates that 9.4 million new cases of TB occurred in 2008 with an estimated 1.3 million deaths in HIV negative people and an additional 500 000 deaths among HIV-positive people [2, 3, 4].

One of the ‘Millennium Development Goals’ from the United Nations Development Programme [5] is to halt and begin to reverse the incidence of TB by 2015. One of the critical issues in achieving this goal is to control the disease by preventing infection and treating the disease as early as possible [6]. Fast and accurate diagnostics have a very important role in this; however in many clinical situations this is not possible as the existing diagnostic methods have serious limitations [7]. Worldwide the majority of TB patients are still diagnosed with tools developed in the 19th Century such as the Tuberculin Skin Test (TST) using Purified Protein Derivative (PPD) and sputum microscopy [6, 8, 9]. The drawback of PPD is the fact that its protein components are shared by many non-tuberculous/environmental mycobacterium families commonly found in developing countries, as well as by the Bacille Calmette-Guérin (BCG) vaccine strains. This significantly decreases the specificity of the TST, since individuals exposed to non-tuberculous mycobacteria or vaccinated with BCG respond immunologically to PPD as well as those who are infected with the tuberculous families (*M. tuberculosis*, *M. bovis*, or *M. africanum*) [10].

MTb recovered from human specimens by microbial culture is today still the gold standard for diagnosing active TB, however the growth of MTb may take from 2 weeks to 2 months and clinicians therefore need to rely on other methods to diagnose patients and initialize treatment [6, 11].

Weaknesses of today’s diagnostic tools lead in general to untreated TB cases, to treatment of patients not infected with MTb, waste of resources and complications from the side effects of anti TB treatment [6]. The development of robust diagnostic tests for detecting latent and active TB is therefore urgently needed.

The tuberculous bacteria contain few specific proteins/antigens that are not present in BCG or most environmental mycobacteria. The ESAT-6 (6 kD Early Secreted Antigen Target) protein and CFP-10 (10 kDa culture filtrate protein) were identified from a *M. tuberculosis* culture filtrate [12, 13]. Both antigens, ESAT-6 and CFP-10 are expressed by the tuberculous mycobacterium families (*M. tuberculosis*, *M. bovis*, and *M. africanum*) but not by any of the BCG-strains and only by few of the atypical mycobacteria (e.g., *M. kansasii*, *M. marinum*, *M. szulgai*) [10, 13].

Based on this knowledge new *in-vitro* diagnostic tests have been developed in the form of T-cell based interferon- $\gamma$  (IFN- $\gamma$ ) assays. These assays use MTb specific antigens (e.g. ESAT-6, CFP-10) and show that T-cells of individuals infected with MTb produce IFN- $\gamma$  when they are exposed to these antigens [14]. The tests show very promising abilities in detecting latent

infection with MTb and were shown to be able to discriminate between patients infected by MTb and BCG vaccinated individuals [13, 15, 16, 17, 18, 19, 20]. The impact of these assays in resource limited countries will however be small due to cost, complexity and the lack of local laboratory infrastructure. [6].

A new tuberculin-like skin test named C-Tb, using a combination of rdESAT-6 and rCFP-10 antigens, has been developed by SSI, Denmark, as a diagnostic test for detecting *M. tuberculosis* infection in man. Following intradermal injection of C-Tb to MTb infected guinea pigs an immune response was formed at the injection site visualised as a cutaneous induration and erythema in TB infected animals. The response is known as local delayed type hypersensitivity (DTH) skin reactions [13, 21, 22]. Both antigens are produced in *Lactococcus lactis*.

The first in man trial with rdESAT-6 alone (TESAT-01) was completed in 2005/2006. It was a dose escalating phase Ia clinical trial conducted at Leiden University Medical College, the Netherlands with 4 doses of 0.01 µg, 0.1 µg, 1 µg and 10 µg administered to groups of healthy volunteers and later 3 doses of 0.01 µg, 0.1 µg and 1 µg were tested in groups of previously treated TB-patients. The aim of this first in man phase I trial was to investigate the safety and the diagnostic potential of rdESAT-6 and to compare it with 2 T.U. Tuberculin PPD RT 23 SSI. The immune response induced in previously treated TB patients was here used as a surrogate marker for a latent infection.

Twenty healthy adults were tested. The rdESAT-6 skin test seemed to be safe in healthy adults in the tested dose range (0.01 to 10 µg). Fifteen previous tuberculosis patients were tested. In this population, 0.01 and 0.1 µg rdESAT-6 seemed safe, whereas, administration of 1.0 µg seemed to be related to more intense and more frequent local reactions at the rdESAT-6 injection site. Only few systemic adverse events were reported, most of these were mild and unrelated to the test administrations.

Based on the results of this study, it was concluded that 0.01 µg and 0.1 µg rdESAT-6 were well tolerated and induced responses at 72± 24 hours of a similar size to 2 T.U. Tuberculin PPD RT 23 SSI. The trial indicated a human dose of rdESAT-6 to be in the range of 0.01 to 0.1 µg/0.1 mL [23, 24]. A dose of 0.1 µg rdESAT-6 was therefore selected for the next phase Ib clinical trial.

Pharmacology studies in guinea pigs showed a risk of sensitisation upon repeated injections of rdESAT-6 visualized by local induration and erythema at the injection site. To address this issue a phase Ib trial (TESAT-02) was conducted at Rigshospitalet, Copenhagen in 2007 to assess the risk of sensitisation upon repeated injections of a fixed dose level of 0.1 µg rdESAT-6 with time intervals of 28, 56 or 112 days, respectively.

31 healthy adults were tested. No serious adverse events occurred and only few adverse events were reported by investigator and all assessed as mild in intensity. The results of this study supported that 0.1 µg rdESAT-6 was safe and well tolerated as seen in the previous phase I study. The results showed a risk of inducing a false positive skin reaction if 0.1 µg rdESAT-6

was injected twice four weeks apart however this risk of sensitisation seemed to decrease with and increased time span between succeeding testing as suggested by previous animal studies [25, 26].

To increase the potential sensitivity of the skin test, experience with IFN- $\gamma$  assays showed that combinations with two or more antigens were necessary for a sufficient sensitivity. As a consequence of these considerations SSI decided in March 2007 to include rCFP-10 to the rdESAT-6 skin test agent without jeopardizing its predicted specificity [13]. The product was named C-Tb. Non-clinical pharmacology studies at SSI confirmed in guinea pigs that the sensitivity increased when rdESAT-6s was mixed with rCFP-10 and similar dose response curves were observed with rdESAT-6 and rCFP-10.

In 2005 Reece et al [27] published that CFP-10 may trigger "Tuberculin shock". He found that 5/10 guinea pigs died 6-36 hours after the skin testing with CFP-10, if the test was done 6 weeks after infection. No deaths were observed if the skin testing was done 4 weeks after infection or earlier. A more likely explanation is that the testing and the deaths were coincidental as the guinea pigs after 6 weeks of infection were at a late stage of disease, where mortality is not infrequent. In a repeat study, no. F1137 [28], conducted at SSI with an infection period of 6 weeks before testing 3/30 (10%) animals died or were about to die from TB even before skin testing. The same number of animals died after skin testing with rCFP-10 or PPD. It is likely that any immunological reagent at this time of disease will be able to induce a shock-like syndrome in an animal.

A bridging toxicity study performed in 2008 with C-Tb concluded that repeated subcutaneous injections of 10  $\mu$ g C-Tb were safe in rats.

The first clinical trial with C-Tb (TESEC-01) was designed to investigate the safety and the risk of sensitisation upon repeated injections of C-Tb in healthy adult volunteers. C-Tb was investigated at two doses of 0.01 and 0.1  $\mu$ g C-Tb. The two doses were injected twice 6 or 12 weeks apart to investigate a risk of sensitisation upon repeated testing. This phase Ia trial was conducted at Rigshospitalet, Copenhagen. No serious adverse events occurred and only few mild adverse events were reported in this first in man clinical trial with C-Tb. Further, it was demonstrated that a second injection of C-Tb can be injected after 6 weeks without inducing a false positive skin reaction. If the time from infection to testing is shorter than the incubation period of TB (=6 weeks) a false negative response to the skin test agents may occur. To rule out an infection during contact tracing and to allow an immune response to develop dual testing 6 weeks apart may therefore be of relevance to a future TB diagnostic skin test [29, 30].

A randomised phase Ib trial (TESEC-02) was initiated in Great Britain in Q1 2010 to determine a safe human dose of C-Tb. As there is no gold standard to identify latent infection, the study was done in individuals within 60 days of starting treatment for active TB. It was anticipated that individuals at an early stage of treatment for active disease may give stronger adverse reactions to C-Tb than individuals with a waning immunity from an infection cured several years before. To be able to market C-Tb in multi-dose vials it is a requirement that the product is preserved. Unpreserved and preserved (0.5 % phenol) formulations of C-Tb were randomly

injected into the left or right arm of each volunteer in a double blind safety and dose finding trial to allow a direct investigation if phenol affects the safety profile and the response of C-Tb.

This trial concluded that C-Tb preserved with 0.5% phenol was safe in patients with active TB and that a dose of 0.1 µg C-Tb gave a skin reaction of a desired size. It was found acceptable to proceed to phase II trials to determine an optimal cut-off point for C-Tb as sign of a TB infection and thus allow calculation of sensitivity and specificity.

The present phase IIa (TESEC-03) trial in a healthy BCG vaccinated population will collect data on the distribution of the induration response, if any, to C-Tb in this population. The specificity of the C-Tb test will be defined as the relative frequency of subjects in a healthy population (i.e., no exposure to MTb) who have an induration response < cut-off after a C-Tb test.

A parallel phase IIb trial (TESEC-04) is planned in patients recently diagnosed with TB +/- HIV to collect data on the distribution of the induration response to C-Tb in these populations. The sensitivity is defined as the relative frequency of patients with an induration response ≥ cut-off in TB patients. The phase IIb clinical trial will be conducted in South Africa in parallel to this phase IIa trial in the United Kingdom.

The optimal cut-off point of being infected will be determined by combining the results from the present specificity study in BCG vaccinated with no previous exposure to MTb with those from a parallel sensitivity study in recently diagnosed TB infected individuals +/- HIV via a Receiver operating characteristic curve.

It is expected that the healthy BCG vaccinated volunteers to be enrolled in the present phase IIa trial will only be subjected to minimal risks of local and systemic adverse reactions following a single intradermal injection of 0.1 µg C-Tb by the Mantoux injection technique. This is based on the non-clinical pharmacology and toxicity studies, previous phase I clinical trials with rdESAT-6 (alone) [23, 24, 25, 26] and two phase I trials with C-Tb, respectively [29, 30].

This protocol has been written in accordance with ICH GCP Topic E 6 [31], ICH Topic E 2A [32] and the EC directives 2001/20/EC [33] and 2005/28/EC [34] of the European Parliament (including underlying guidance).

